### Study design

We will conduct a non-randomized stepped wedge study [46]. Participants can choose to either start the program within 4 weeks after inclusion (early starters) or after 8 to 10 weeks (late starters). The late starters allow us to collect control data about participants who have not yet followed the program [47]. See Fig. 1 for an overview of the non-randomized stepped wedge design.

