### Measurements

In the SMART study, we will take the following measurements:Questionnaire study. All participants will fill in an online questionnaire at three moments: right after inclusion (baseline), after 8 weeks and after 16 weeks. Completion of a questionnaire will take approximately 20 minutes. A written questionnaire can be provided if preferred. We will use both validated and self-constructed questionnaires (for an overview of the measures, see Table 4).Logbooks. After each meeting, participants will be asked to answer a set of questions in a logbook: What did you learn during the meeting? In what way was the meeting useful (if at all)? How was the group experience? Which exercises were useful? Participants will be asked to document their action plans.Recorded video-conferencing sessions. The group meetings will be video recorded with the consent of the participants.

**Table 4 Tab4:** Measurements tools

Measurement tools	
Concept	Measured by
Primary outcome:	
Self-management behavior	Health Education Impact Questionnaire (HEIQ) [30] **Patients and relatives:** Subscale ‘constructive attitudes and approaches’ (*5 items)*
Secondary outcomes:	
Self-management behaviors	Health Education Impact Questionnaire (HEIQ) [30] **Patients:** Subscales ‘skill and technique acquisition’ (*4 items)*, ‘health services navigation’ (*5 items)*, ‘social integration and support’ (*5 items)* **Relatives:** Subscales ‘health directed behavior’ (*4 items)*, ‘positive and active engagement in life’ (*5 items)*, ‘social integration and support’ (*5 items)*
Quality of life	**Patients:** McGill Quality of Life (MQOL) [31, 32] (*18 items)* **Relatives:** Quality of Life in Life Threatening Illness Family Carer Version (QOLLTI-F) [33] Subscale ‘overall quality of life’ (*1 item)*
Self-efficacy	**Patients:** Self-efficacy for managing chronic disease [24] Adaptation to advanced cancer *(6 items)* **Relatives:** Self-efficacy caregivers short adaption [34] Adaptation to advanced cancer (*7 items)*
Symptoms	**Patients and relatives:** Fatigue numeric rating scale (NRS) (*1 item)* **Patients:** Pain numeric rating scale (NRS) (*1 item)* **Relatives:** Stress numeric rating scale (NRS) (*1 item),* Sleep numeric rating scale (NRS) (*1 item)*
Caregiver burden	**Relatives:** Caregiver Reaction Assessment Dutch (CRA-D) [35]; Subscale ‘impact on schedule’ (*5 items)*
Depression and Anxiety	**Patients and relatives:** Hospital Anxiety and Depression (HADS) [36] *(14 items)*

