### Sample size calculation

To show an effect size of at least 0.5 SD on the HEIQ scale “constructive attitudes and approaches” [51], with a power of 80% and a significance of 0.05, assuming an individual autocorrelation across different time points of 0.7 [51], and assuming an average cluster size of eight patients simulation showed that in total 104 patients would need to be included across a wide range of within-period ICCs. With an expected drop-out rate of 20% (similar to the various CDSMP programs [24–26]), we need to recruit at least 130 patients. Based on our pilot study, we expect that of the participants, 20% will be relatives, therefore, we expect to include at least 32 relatives. In total, we will include 162 participants.

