### Statistical analysis

We will follow the intention-to-treat principle for the analyses of the primary and secondary outcomes. Descriptive statistics will be used to summarize patient characteristics (age, gender, ethnicity, Social Economic Status, marital status, cancer type and time since diagnosis).

For the patient outcomes, we will use linear mixed models with a random intercept to adjust for repeated measures over time. As fixed effects, we will include time points of measurement (baseline, 8 weeks and 16 weeks) and a variable denoting when the participant received the program at each time point (early versus late starters). To adjust for possible confounding, we additionally will add age, sex, ethnicity, Social Economic Status, cancer type and time since diagnosis as fixed effects to the model.

Furthermore, we will assess whether there is a dose-response relationship between the number of sessions of the program and outcome. We will perform a similar analysis as for the main effect, but include the number of sessions instead of the intervention group.

The quantitative data analyses for relatives will be conducted in a similar way but it will have an explorative nature due to its expected lower number of participants.

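### The primary model names a random intercept as its only within-person term, so its standard error rests on equal variances and equal correlations across visits that could cheaply be left unassumed

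*Protocol article*

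**What the plan says.** The Statistical analysis section of the protocol article sets the within-person part of the patient model in one clause: "we will use linear mixed models with a random intercept to adjust for repeated measures over time". The fixed part has a categorical time effect for the three visits, covariates for confounding, and a program term, worded as "a variable denoting when the participant received the program at each time point (early versus late starters"). No random slope, residual covariance structure or robust standard error is named, and the section does not say that residuals are independent with equal variance.

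Questionnaires are completed on three occasions, namely "right after inclusion (baseline), after 8 weeks and after 16 weeks". On timing of the program, the Study design section reads: "Participants can choose to either start the program within 4 weeks after inclusion (early starters) or after 8 to 10 weeks (late starters").

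In the Sample size calculation section, the target is a difference of 0.5 SD with 80% power at the 0.05 level. The repeated measures enter that calculation through a single value, "assuming an individual autocorrelation across different time points of 0.7". The result is 104 evaluable and 130 recruited patients.

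**The concern.** A random intercept with independent, equal-variance residuals forces compound symmetry: one variance at every visit and one correlation between every pair of visits. Correlations between repeated measurements often fall as the interval grows, and the variance may differ between visits. If either happens, the model-based standard error of a within-person contrast is wrong.

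The contrast matters here. If the program variable is time-varying (early starters 0,1,1; late starters 0,0,1), the two groups differ in exposure only at week 8. The program effect is then the week-8 group difference, corrected by the differences at baseline and week 16, and its standard error depends directly on the assumed covariance. At stake are the width of the primary confidence interval and the level of the primary test. The article applies the same model family to the secondary outcomes, the dose-response analysis and the exploratory analysis of relatives.

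**Working it through.** **The plan's own figures.** 104/(1 − 0.20) = 130, as stated. The 104 can be neither reproduced nor refuted, because the range of ICCs, the between-period cluster correlation and the simulated model are not given.

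**Inputs.** From the article: three visits, correlation 0.7, effect 0.5 SD, alpha 0.05, 104 evaluable patients. Assumed: a two-sided test; 52 early and 52 late starters (the ratio is not given, but it cancels from the standard-error ratios); exposure 0,1,1 and 0,0,1; complete data; no peer-group effect; and every covariance pattern other than constant 0.7 with equal variance. Variances are in units of the baseline variance.

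**Formulas.** Let D0, D8 and D16 be the early-minus-late differences in means. With free time effects, the random-intercept model fits the average variance s² and average correlation ρ over visits, and estimates

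- effect = D8 − k(D0 + D16), with k = ρ/(1 + ρ);
- reported variance = (2/52) × s²(1 − ρ)(1 + 2ρ)/(1 + ρ);
- true variance = (2/52) × [v8 + k²(v0 + v16 + 2c0,16) − 2k(c0,8 + c8,16)], where v and c are the true variances and covariances.

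Type I error is 2Φ(−1.96 × reported SE/true SE).

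**Constant correlation 0.7, equal variances.** 0.3 × 2.4/1.7 = 0.4235 by both formulas, so the SE is √(0.4235/26) = 0.128. The ratio is 1.00 and type I error 5%.

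**Correlation 0.7 over 8 weeks, 0.49 over 16.** ρ = (0.7 + 0.7 + 0.49)/3 = 0.63 and k = 0.3865. Reported: 0.37 × 2.26/1.63 = 0.513, SE 0.140. True: 1 + 0.1494 × 2.98 − 2 × 0.3865 × 1.4 = 0.363, SE 0.118.

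**Week-8 SD 1.3 times the others (variance 1.69), correlation 0.7.** s² = 3.69/3 = 1.23; average covariance (0.91 + 0.91 + 0.70)/3 = 0.84; ρ = 0.683; k = 0.4058. Reported: 1.23 × 0.3171 × 2.3659/1.6829 = 0.548, SE 0.145. True: 1.69 + 0.1647 × 3.4 − 2 × 0.4058 × 1.82 = 0.773, SE 0.172.

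| Assumed pattern | Reported/true SE | Type I error |
|---|---|---|
| Constant 0.7, equal variance | 1.00 | 5.0% |
| 16-week correlation 0.6 | 1.09 | 3.2% |
| 16-week correlation 0.49 | 1.19 | 2.0% |
| Week-8 variance ×1.25 | 0.93 | 6.9% |
| Week-8 variance ×1.5 | 0.87 | 8.7% |
| Week-8 variance ×1.69 | 0.84 | 9.9% |
| 0.49 and week-8 variance ×1.5 | 0.98 | 5.4% |
| Variances 1, 1.25, 1.5; correlation 0.7 | 1.01 | 4.8% |

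REML simulation gave the same directions. With N = 104 complete, and with N = 130 and 20% dropout, the ratios were 1.18 and 1.16 under fading to 0.49, and 0.90 and 0.89 under week-8 variance ×1.5.

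**Coding of the program variable.** Adding an early/late main effect to the exposure gives ratios of 1.27 (fading to 0.49) and 0.92 (week-8 variance ×1.5). A group-by-time model read at week 8 gives 1.11 and 0.96. A fixed early/late label gives exactly 1.00 throughout: the comparison then averages over visits, and its variance depends only on the average variance and covariance, which the random intercept fits.

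**Power at the planned effect.** Under fading to 0.49, Φ((0.5 − 1.96 × 0.140)/0.118) is about 97%, before any peer-group clustering.

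**Efficiency.** An unstructured covariance would lower the true SE by about 3% under fading to 0.49 and 2.4% under week-8 variance ×1.5. The harm is mainly a misreported SE rather than a poor estimator.

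**The case against.** The strongest reply is that the article does not say the random intercept is the only structure. A mixed model can carry a random intercept and a structured residual covariance, and a condensed article may leave that to the full protocol or SAP. This stands: the text names one term, but it does not exclude others.

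Second, the plan is consistent with itself. One correlation of 0.7 across time points is what a random intercept implies, and with equal variances the interval is correct. This stands too, although a planning value does not show that the correlation will be constant.

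Third, the failure patterns come from this review. The Discussion mentions disease progression as a cause of dropout and says nothing about the covariance of the outcome. Inflated type I error needs extra variance specific to week 8; a steady rise across visits leaves the ratio near 1. This limits the size of the point.

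Fourth, the coding of the program variable is unclear. The gloss of early versus late starters, and the later reference to an intervention group, allow a fixed label, for which the problem disappears. But a fixed label compares the two groups averaged over all visits, including those where both have the same exposure, so it does not isolate the program effect. The reference to each time point, and the use of late starters as controls before they start, favor a time-varying variable.

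A reader might infer that the primary interval and p-value are wrong, or that the study is underpowered. The documents support neither. They give no covariances by visit, the two departures can offset each other, and fading alone leaves power far above 80% at 0.5 SD before clustering. A power loss can be shown at smaller effects, but those are not the planned effect.

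**Conclusion.** The point holds as a conditional robustness concern, not as a demonstrated error. As written, the primary standard error relies on equal variances and equal correlations across three visits, an assumption the design does not need. For a time-varying program variable, plausible departures move the reported SE from 19% too large to 16% too small, with type I error between 2.0% and 9.9%. Fading correlation makes the test conservative; only extra variance at week 8 threatens its level. These figures rest on the assumed covariance patterns, equal allocation, the 0,1,1 / 0,0,1 exposure, complete data and no peer-group effect. A cheap improvement is worth making.

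**What to change.** In the Statistical analysis section, or in the SAP if one exists, replace the random intercept for repeated measures by an unstructured 3x3 within-patient covariance over baseline, week 8 and week 16. Fit by REML with Kenward-Roger or Satterthwaite degrees of freedom; with normal critical values the unstructured model rejected in 4.7% to 6.6% of simulated null trials. Keep any peer-group effect as a separate term. Prespecify a simpler fallback for non-convergence, such as a random intercept with heterogeneous AR(1) residuals. State at the same time whether the program variable is time-varying, because the effect of the covariance choice depends on it.

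The cost is a change of wording, six covariance parameters instead of two, and about 1% in SE (by simulation) if the random-intercept structure is true. Three fixed visits and about 104 patients support this comfortably. For the relatives, with about 32 expected, the fallback may be needed more often.

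### The program term in the primary model is described in conflicting ways, and the model has no term to absorb differences between self-selected early and late starters

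*Protocol article*

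**What the plan says.** The Statistical analysis section of the protocol article gives the primary model as a linear mixed model with a random intercept. Its fixed effects are the three measurement times and "a variable denoting when the participant received the program at each time point (early versus late starters". Six confounders are added: age, sex, ethnicity, socioeconomic status, cancer type and time since diagnosis. No interaction and no second program or group term is listed. The dose-response paragraph refers back to the same term when it says the model will "include the number of sessions instead of the intervention group".

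Under Study design, participants choose their own start, within 4 weeks of inclusion or after 8 to 10 weeks. Its stated purpose for the second group is: "The late starters allow us to collect control data about participants who have not yet followed the program". Questionnaires fall at baseline, week 8 and week 16.

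**The concern.** The wording supports two different models. A variable defined separately at each measurement occasion is the usual stepped-wedge exposure: early starters 0/1/1, late starters 0/0/1. A variable whose levels are early and late starters, and which is later called a group, is constant within a person. The two codings give different coefficients, and the article does not say which one is the program effect.

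A second issue remains whichever coding is used. Start time is self-chosen, so the two groups may differ for reasons unrelated to the program. Neither coding includes a term that separates such a difference from the program effect. The six listed confounders do not include baseline function or self-management, which could plausibly influence the choice of start.

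At stake are the size and power of the primary estimate. An undefined program coefficient also leaves the choice open until the data have been seen.

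**Working it through.** **The plan's own figures.** The sample size section gives these inputs:
- "To show an effect size of at least 0.5 SD on the HEIQ scale"
- "with a power of 80% and a significance of 0.05" (two-sided assumed)
- "assuming an individual autocorrelation across different time points of 0.7"
- "assuming an average cluster size of eight patients"

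Its result is that "in total 104 patients would need to be included across a wide range of within-period ICCs". The dropout step reproduces: 104/0.8 = 130. The 104 cannot be uniquely reproduced, because the ICC range, the between-period decay of correlation and the share of early starters are not given. A search in steps of 8, with a 50:50 split and ICC from 0 to 0.2, gives these required totals:
- Exposure term: 56 at every ICC without decay; 56 to 128 with decay 0.7.
- Exposure plus group: 64 without decay; 64 to 136 with decay 0.7.
- Fixed group diluted to 0.5/3: 912 at ICC 0; 2176 to 2488 at ICC 0.2.
- Fixed group carrying the full 0.5 SD: 104 at ICC 0, but 248 to 280 at ICC 0.2.

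A figure of 104 that holds over a wide range of ICCs is therefore plausible for an exposure term and does not fit a fixed group.

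**Set-up for the four estimators.** Assume 52 early and 52 late starters, correlation ρ = 0.7 and no clustering. Let D0, D8 and D16 be the early-minus-late mean differences, δ = 0.5 the program effect, and b a stable difference between the groups. With the effect fully kept, (D0, D8, D16) = (b, δ + b, b). The variance factor is 1/52 + 1/52 = 0.03846. Power is Φ(estimate/SE − 1.96).

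1. Time + fixed group: (D0 + D8 + D16)/3 = δ/3 + b.
   - With b = 0 this is 0.167. Variance 0.03846 × (1 + 1.4)/3 = 0.03077, SE 0.175. Power Φ(0.95 − 1.96) = 16%.
   - With δ = 0 and b = 0.3: Φ(1.71 − 1.96) = 40% false positives.
2. Time + exposure: D8 − [ρ/(1+ρ)](D0 + D16) = D8 − 0.412(D0 + D16) = δ + b(1−ρ)/(1+ρ) = 0.5 + 0.176b.
   - Variance 0.03846 × 0.3 × 2.4/1.7 = 0.01629, SE 0.128. Power Φ(3.92 − 1.96) = 97.5%.
   - With b = 0.3 the leak is 0.053 SD, a shift of 0.41 SE. Type I error is Φ(0.41 − 1.96) + Φ(−0.41 − 1.96) = 7%.
3. Time + exposure + group: D8 − (D0 + D16)/2 = δ, free of b.
   - Variance 0.03846 × 0.3 × 1.5 = 0.01731, SE 0.132. Power Φ(3.80 − 1.96) = 97%.
4. Group-by-time contrast, change from baseline to week 8: D8 − D0 = δ, free of b.
   - Variance 0.03846 × 0.3 × 2 = 0.02308, SE 0.152. Power Φ(3.29 − 1.96) = 91%.

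A 300-run mixed-model simulation at N = 104 agreed for the first two: mean 0.166 with power about 18%, and mean 0.500 with power about 99%.

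**If early starters lose some of the effect by week 16**, with b = 0:

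| Share kept | D16 | Fixed group | Exposure | Exposure + group | Baseline to week 8 |
|---|---|---|---|---|---|
| all | 0 | 0.167 | 0.500 | 0.500 | 0.500 |
| half | −0.25 | 0.083 | 0.603 | 0.625 | 0.500 |
| none | −0.5 | 0 | 0.706 | 0.750 | 0.500 |

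**The case against.** The strongest reply is that the quoted phrase already contains an exposure term. A starter label cannot vary by measurement occasion, the design is a stepped wedge, and late starters are said to serve as controls before they take part. The sample size statement points the same way. This stands. A reader might infer that the plan has no exposure term and that its primary analysis will recover only a third of the effect. The documents do not support that: it follows only from the less likely coding, and the one-third figure itself depends on equal baselines and a fully kept effect.

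Second, under exposure coding the remaining bias is small. The 0.3 SD difference is an assumption, it would have to persist after adjustment for six covariates, and the Discussion already acknowledges residual confounding. This also stands as to size. But acknowledging the risk does not remove it, and a group term removes the stable part at little cost.

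Third, a journal article may leave 0/1 coding to a fuller document. That would excuse silence. Here the article does describe the term, and its descriptions conflict.

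**Conclusion.** The program term of the primary model is inconsistently defined and should be restated before analysis. A time-varying exposure is probably intended. With that coding, equal baselines and a sustained effect, the full 0.5 SD is recovered, and power without clustering is about 97%. The fixed-group coding that the wording also permits would give at most 0.167 SD and power about 16% under the stated assumptions, with any baseline difference added in full.

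Under the likelier coding the defect is modest but avoidable: 17.6% of any stable residual difference between self-selected groups enters the estimate. That fraction depends on the correlation of 0.7 and not on the share of early starters. The standard errors do depend on the assumed 50:50 split and on ignoring clustering. None of this shows that 104 patients is wrong, since the inputs needed to check it are not given.

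**What to change.** State the fixed effects as time (three levels), early/late starter group, and a time-varying exposure indicator coded 0/1/1 for early and 0/0/1 for late starters, plus the listed confounders. Name the exposure coefficient as the program effect, and say that the group term only absorbs self-selection. In the dose-response paragraph, say that the number of sessions replaces the exposure indicator, not the group term.

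The cost is wording and a standard error about 3% larger (0.132 against 0.128). The group term removes only differences that are constant over time.

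This model assumes that early starters keep the effect to week 16; if half is kept it returns 0.625 SD instead of 0.5. So also report, from a group-by-time model, the contrast for change from baseline to week 8. It does not need that assumption but is less precise (SE 0.152, power about 91%). The two are not interchangeable, so the plan should say in advance which one is the primary estimate.

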Loneliness	**Patients and relatives:** University of California, Los Angeles (UCLA) loneliness scale [37] Short version *(3 items)*
Other measures:	
Healthcare utilization	**Patients and relatives:** Number of contacts with healthcare professionals, number of hospitalization days, reasons for hospitalization, number of visits to accident and emergency departments [38] Self-constructed (*6 items)*
Sociodemographic characteristics	**Patients and relatives:** Age, gender, ethnicity, Social Economic Status (SES), marital status, cancer type and time since diagnosis Self-constructed (*15 items)* **Relatives:** Hours of caregiving per week *(1 item)*
Comorbidity	**Patients and relatives:** Self-Administered Comorbidity Questionnaire (SCQ) [39] *(1 item)*
Health literacy	**Patients and relatives:** Degree of understanding medical information, Set of Brief Screening Questions (SBSQ) [40] *(3 items)*
Resilience	**Patients and relatives:** Connor-Davidson Resilience Scale (CD-RISC) [41] *(10 items)*
Digital comfort and skills	**Patients and relatives:** The comfort and skills of using computer and mobile devices [42] (*2 items)*
Group cohesion	**Patients and relatives:** The Group Climate Questionnaire (GCQ-23) [43] *(23 items)*
Evaluation of the program	**Patients and relatives:** Experiences with the program Self-constructed (*7 items)*

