Our SMART study has several risks. The study population and the program contain several factors that cannot be fully controlled. Firstly, there will be a considerable risk of drop out, either partly (some meetings) or completely, to disease progression or treatment burden of our vulnerable population [59]. To minimize this, we only include patients with a WHO performance status of 0 or 1 [60], and participants can choose when to start with the program to accommodate their schedule. Secondly, the risk of selection bias cannot be ruled out. Conducting research through self-referral, by online questionnaires and the video-conferencing group format, may primarily attract participants with higher digital literacy [61]. To minimize this risk, we offer technical support before and during the program, and explicitly explain that experience with video-conferencing applications is not necessary. Banbury and colleagues demonstrate that inexperience with video-conferencing or computer use was not a major problem for participation in video-conferencing groups [22]. Thirdly, while a randomized controlled trial (RCT) is preferred as a gold standard for measuring the effects of an intervention, we opt for a non-randomized stepped wedge design to make the study better feasible. Whilst we adjust for possible confounders in the analysis, residual confounding still remains a risk. Fourth, our program is a complex intervention, meaning it contains several interacting components, such as improving self-efficacy and behavior, the self-tailoring format, and group interaction [62]. Therefore, it may be difficult to identify the active components of the program. Combining the quantitative data of this study with the findings of our complementary qualitative study will provide insight into participants’ experiences and the perceived working mechanism of the program.

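### Start time is self-chosen, but the fixed confounder set leaves out baseline health and psychological measures that the trial collects

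*Protocol article*

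**What the plan says.** **Allocation.** Under Study design the article states: "Participants can choose to either start the program within 4 weeks after inclusion (early starters) or after 8 to 10 weeks (late starters". The Discussion gives the reason, among the measures against drop-out: "participants can choose when to start with the program to accommodate their schedule".

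**Model.** For patient outcomes the Statistical analysis section plans "linear mixed models with a random intercept to adjust for repeated measures over time". The fixed effects are time point (baseline, 8 and 16 weeks) and "a variable denoting when the participant received the program at each time point (early versus late starters". For confounding it adds: "we additionally will add age, sex, ethnicity, Social Economic Status, cancer type and time since diagnosis as fixed effects to the model". This is a definite list, set out in the article itself.

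**Data collected.** The Measurements section says: "All participants will fill in an online questionnaire at three moments: right after inclusion (baseline), after 8 weeks and after 16 weeks". Table 4 includes HADS, self-efficacy, pain and fatigue ratings, comorbidity, resilience, health literacy, digital comfort and healthcare use. None of these is in the adjustment set. WHO performance status appears only as an eligibility criterion (0 or 1).

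**Acknowledgement.** The Discussion accepts that residual confounding remains a risk. It gives no reason for leaving these measures out.

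**The concern.** At week 8 the early starters have had the programme and the late starters have not. That contrast carries most of the between-group information on the effect, and the participants themselves decide who is on which side of it. Current symptoms, distress or confidence could affect when someone chooses to begin. They could also affect how constructive attitudes and approaches, the primary outcome, develop over the next weeks. The Background itself calls self-efficacy a key factor in improving self-management.

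The six listed covariates describe demography and disease history and say little about these states. Any imbalance in them would be credited to, or subtracted from, the programme. The primary conclusion is at stake, in the part of the analysis meant to protect it.

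**Working it through.** **The plan's own figure.** 104 evaluable patients with 20% drop-out gives 104 / (1 − 0.20) = 130, as stated. This does not bear on confounding; 104 is used below only for the standard error.

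**Inputs from the article.** Autocorrelation ρ = 0.7, target 0.5 SD, 104 evaluable patients (Sample size calculation); time points 0, 8 and 16 weeks; random-intercept model (Statistical analysis).

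**Assumed inputs.** Exposure is time-varying: early 0, 1, 1 and late 0, 0, 1. Starters split evenly, 52 and 52, with no group-level clustering. One omitted covariate differs by d = 0.5 SD between early and late starters, net of the listed covariates. Its slope on 8-week change is 0.2 SD per SD. The article supports neither the 0.5 nor the 0.2; they are illustrations.

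**Formula.** Once the period effects are fitted, the two exposure patterns differ only at week 8. Let y0, y8 and y16 be the early-minus-late gaps in mean outcome caused by the covariate alone. Generalised least squares with an exchangeable correlation ρ gives

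bias = y8 − [ρ / (1 + ρ)] × (y0 + y16), with ρ / (1 + ρ) = 0.7 / 1.7 = 0.412.

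**Covariate acting on change.** The week-8 gap is 0.5 × 0.2 = 0.10 SD.

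| Influence by week 16 | y0, y8, y16 | Bias (SD) |
|---|---|---|
| Gone | 0, 0.10, 0 | 0.100 |
| Persists | 0, 0.10, 0.10 | 0.10 − 0.041 = 0.059 |
| Keeps growing linearly | 0, 0.10, 0.20 | 0.10 − 0.082 = 0.018 |

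**Covariate acting on level only.** With a constant gap g, bias = g × (1 − 2 × 0.412) = 0.176 g. For level slopes of 0.2 and 0.5 SD, g = 0.10 and 0.25, so the bias is 0.018 and 0.044 SD. The share passed on is (1 − ρ) / (1 + ρ): 0.33 at ρ = 0.5 and 0.11 at ρ = 0.8.

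**Against the precision of the trial.** SE = √[(2/52) × (1 − ρ) / (1 − ρ/(1 + 2ρ))] = √[0.0385 × 0.3 / 0.708] = 0.128 SD. Type I error is Φ(−1.96 + bias/SE) + Φ(−1.96 − bias/SE). For biases of 0.018, 0.059 and 0.100 SD this is about 0.052, 0.075 and 0.123, against a nominal 0.05.

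**What adjustment removes.** The same model was refitted with the covariate added in two ways:

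| Case | Unadjusted | Main effect only | With covariate-by-time terms |
|---|---|---|---|
| Change, gone by week 16 | 0.100 | 0.094 | 0 |
| Change, persists | 0.059 | 0.047 | 0 |
| Change, linear | 0.018 | 0 | 0 |
| Level only | 0.018 to 0.044 | 0 | 0 |

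Baseline is itself an outcome row, so a main effect corrects a stable gap but not a gap that opens after baseline. With time terms the variance rises by the factor 1 + d²/4 = 1.0625, and the SE becomes 0.128 × √1.0625 = 0.132 SD. The zeros assume a covariate measured without error and a linear effect.

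**The case against.** The strongest reply is that the design already absorbs most stable differences. Baseline is an outcome and each patient has a random intercept, so at ρ = 0.7 only about 18% of a constant gap reaches the programme effect. This stands, and it is why the level-only bias is small. Restriction to WHO status 0 or 1 narrows the health differences further. The Discussion admits residual confounding, and the choice of covariates is partly judgement. Admitting the risk does not, however, explain leaving relevant measures in hand unused.

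A reader might infer more than the article supports in four places:

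- **That distress or perceived need drives the choice.** The article documents only schedule.
- **That the planned estimate is off by 0.10 SD, a fifth of the target.** That is the week-8 gap. It equals the model's bias only if the influence has gone by week 16, and it is the top of the three cases.
- **That a whole level gap enters the estimate.** This would need exposure coded as a fixed early/late label. The bracketed words allow that reading, but the same phrase ties the variable to each time point. It is a separate question of wording.
- **That performance status and recruitment route are ready for use.** The article describes an eligibility limit and two recruitment routes, but does not say that either is recorded as an analysis variable.

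It is also fair to object that simply lengthening the list of main effects would not do the job. The refit confirms this, and the remedy below reflects it.

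**Conclusion.** The point holds in moderate form. The adjustment set is fixed, it is confined to demographic and disease descriptors, and it omits collected measures that are plausible confounders of a self-chosen start. Under the assumed inputs the bias is about 0.02 to 0.10 SD for a covariate acting on change, or 4% to 20% of the 0.5 SD target, and about 0.02 to 0.04 SD for a stable level difference. Its direction is unknown.

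These sizes rest on time-varying exposure, ρ = 0.7, an even split and a single covariate. They illustrate what could happen and do not show that the estimate will be biased. The plan should be changed, but the flaw does not invalidate the design.

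**What to change.** Prespecify, before outcome data are examined, a short set of pre-programme covariates taken from the baseline questionnaire. Examples are HADS, self-efficacy, resilience, pain and fatigue ratings, and comorbidity. Alternatively, build one propensity score for early start from them.

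- Enter the set, or the score, with covariate-by-time interactions, or use the score as weights. Main effects alone are not enough.
- HADS, self-efficacy, pain and fatigue are secondary outcomes. Leave each out of the model in which it is itself the outcome, and out of any score used there.
- Confirm that resilience and comorbidity are asked at baseline; the article does not list instruments by time point.
- Add WHO performance status and recruitment route only if they are recorded.

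**Cost.** No new questionnaire is needed. Each covariate or score with time terms takes three parameters (one main effect and two interactions). One score therefore costs 3, and six covariates counted singly would cost 6 × 3 = 18 with 104 evaluable patients, which favours the score or a very short list. The SE rises from about 0.128 to 0.132 SD for one covariate or score under the assumptions above. Confounding by unmeasured factors remains, and the existing caveat in the Discussion should stay.
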